### Inclusion criteria

Study participants for Phase-I: Registered nurses working in selected hospitals will be included in the study. The hospitals will be selected based on the convenience of the researcher.

For Delphi technique: Five to seven experts in the field of forensic science and forensic nursing will be selected.

Study participant for Phase-II: Female registered nurses from 22 to 45 years working in a tertiary care hospital will be included in the study.

### Data collection

Phase-I: Delphi method to finalise the content of the SANE-GP training module. Permission from the respective hospital management will be obtained before the advertisement for the recruitment of nurses to the study. The study process will be informed in detail through an information sheet, and informed consent will be obtained from the participants during Phase-I. The researcher will be present throughout the data collection. Phase-I of the study also contains the development of a training module; a Delphi method will be used to finalise the content of the SANE-GP training module.

The researchers will do a literature search and prepare the initial draft of the module and the knowledgeable subject experts in DAC will assess the readability of the initial draft. Revisions will be made on the draft module based on their suggestions. When the expert panel list is finalized, a discussion forum will be setup on an online platform by keeping the details of the experts anonymous. The draft module and the other the questionnaire will be made available to the experts either through email or uploading to the online forum. A stage one of Delphi will be initiated and the experts will go through the draft module and assess based on questionnaire. The questionnaire involves items such as whether the content is worded correctly, whether the content is relevant, and whether the content is adequate. All the items have to be graded using a four-point Likert rating scale. The experts will have one-month time to the overall assessment of the draft module. When the responses (Scores and comments) from all the panel experts are available then it will be scrutinised by the researchers and identifies the common and conflicting viewpoints. The draft module will be revised based on the suggestions by the expert panel. The stage one of the Delphi ends with preparation for the stage two. In the stage two of Delphi the scores and the comments from the experts are mailed to the experts and the experts are encouraged to revise their earlier views in light of the replies of other members of the group. The experts will grade the draft module based on the items in the questionnaire and the disagreements will be resolved by discussing and negotiating with the experts. The draft module will be further revised and move forward for the final stage of Delphi. The process will be repeated until all the panellists in the Delphi reach a consensus. A thematic framework will be used for the analysis of the information collected through the Delphi method.

Phase-II: The effectiveness of the SANE-GP will be assessed through administering KQSANE-I. A pretest will be conducted on day one, and an immediate post-test will be conducted after the intervention. Follow-ups will be conducted on the 8th, 16th, and 24th week after SANE-GP. The skill of the participants in performing SAE will be assessed after the completion of each section of the module through a skill checklist. After the implementation of SANE-GP, the participants will be randomly picked for assisting the forensic expert whenever a sexual assault victim is coming to the hospital for examination. The implementation of the SANE-GP will be assessed by assessing the practice of the nurses by the forensic expert (outcome assessor) through a checklist.

### Data collection instruments

*Tool 1: Demographic Proforma*

Demographic proforma includes items such as age, gender, occupation, highest education, years of experience, specialty, and previous experience in SAE.

*Tool 2: KQSANE-I*

This will be used for assessing the knowledge of participants regarding the sexual assault examination. The tool will be developed in Phase-I after completing all tool development steps, namely, item development, item pooling, content adequacy assessment (clarification of the items and refining the items), the administration of the questionnaire (empirical testing after determining the scale for items and adequate sample size), item analysis, reliability assessment and assessing construct validity.

### SANE grounding program (SANE-GP)

The SANE-GP will have multiple teaching-learning activities given to the participants for a period of one week. Each session will last for 45 min and seven sessions will be conducted per day. The content of each module and the order of the sessions also will be finalized after the third stage of the Delphi. Additional modules will be also added based on the suggestions of the expert panel. The details of the modules which will be prepared and send to the panel experts are mentioned below.
1.
**Overview of forensic and sexual assault examination**
i.
*History of medico-legal examination*
ii.
*The constitution of India and human rights*
iii.
*Criminal behaviour and criminal body language*
2.
**Male, female, intersex and ambiguous genitalia**
3.
**Medico-legal history taking**
i.
*Communication and soft skill development (for caring of victims)*
ii.
*Sexual abuse against children*
iii.
*Sexual violence against transgendered persons, intersex persons, and persons with alternative sexual orientations (ASO)*
iv.
*Sexual violence against elderly*
v.
*Prerequisites for history collection and examination*
4.
**Observing and assessing physical examination findings**
i.
*Local examination of genital parts and other orifices*
5.
**Medico-legal evidence collection**
i.
*Informed consent*
ii.
*Evidence and types of evidence*
iii.
*Crime scene investigation*
iv.
*Sexual assault forensic examination (SAFE) kit*
v.
*Body evidence and anogenital evidence collection*
vi.
*Collection and packing, and preservation of material evidence from the survivor*
vii.
*A chain of custody*
6.
**Forensic photography, colposcopy, and other digital evidence**
i.
*Cameras and accessories*
7.
**Medical management of cases with sexual violence**
i.
*Standard operating protocol*
8.
**Sexually transmitted infection testing and prophylaxis**
9.
**Pregnancy testing and prophylaxis**
10.
**Medico-legal documentation**
i.
*Examination of injuries and intimation to police*
11.
**Legal consideration and judicial proceedings**
i.
*The Criminal Law Amendment Act 2013*
ii.
*The Indian Evidence Act 1872*
iii.
*The CrPC and the Indian Penal Code*
iv.
*The Protection of Children from Sexual Offences Act, 2012 (POCSO Act)*
v.
*Legal responsibilities of health professionals*
12.
**Community collaboration**
i.
*Dealing with police and judiciary and child welfare committee*
ii.
*Dealing with public and mass media*
13.
**The psychosocial care of victims and family members**
14.
**Networking of SANE nurses**

The SANE-GP also includes practical activities such as case discussions, discussion of supreme court and trial court verdicts, communication and soft skills demonstrations, documentation of injuries, mock case examinations, simulations, dummy examination, and preparation of slides with the specimen collected from the vaginal vault and other orifices using swabs.

### Ethical consideration

Institutional Ethics Committee of Kasturba Hospital and Kasturba Medical College Manipal, Karnataka, India, approved the proposed study through wide reference No 653/2018. Complete information about the study will be given to the participants through an information sheet and written informed consent will be obtained (see
*Extended data,*
[name] *et al*., 2022b, c, d).

### Expected outcomes

The current study is aimed at assessing the knowledge, skill, and practice of nurses regarding sexual assault examination. The knowledge will be assessed before SANE-GP, and three follow-ups will be conducted on the 8th, 16th, and 24th week after SANE-GP. The researchers will meet the participants in their work area and administer the questionnaires physically. The skill will be assessed immediately after the completion of each module in the SANE-GP whereas the practice of the participants will be assessed randomly in the presence of the forensic expert from the research setting using a practice checklist. Once the participants complete the SANE-GP, they will be enrolled in an association registered under the Societies Registration Act, 1860. This platform will be used for the communication and future development of SANE programs in India.

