### The study

The proposed research is designated to determine the level of the nurse’s competence and knowledge in the examination and management of sexual assault and investigate the effectiveness of multicomponent training in improving knowledge and skill. Implementation of multicomponent training enables nurses to communicate efficiently, examine precisely, collect and preserve evidence accurately and present it properly before the court of law.

The increase in the number of sexual crimes against women and children, stringent guidelines and protocols issued by the government, the influence of mass media, and increased social pressure demands health care professionals to be more accurate and sensitive in handling cases of sexual assault. The findings of the study will help to develop a protocol for nurses, and the same can be utilised as a model guideline for nurses in India. The findings of the study are expected to initiate the sexual assault nurse examiners network (SANE network) in the Udupi district, which can be adopted to other districts.

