### Research objectives

i.Develop a valid and reliable instrument to measure the knowledge regarding SAE among nursesii.Develop a SANE-GP module using a three-stage Delphi methodiii.Explore the effectiveness of SANE-GP on the knowledge and skill regarding SAE.iv.Develop a platform for the SANE network in the country

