## Protocol

### Design

The proposed study adopts a cross-sectional survey design in Phase-I and an experimental design to meet the objectives in Phase-II. The study also uses a Delphi technique for the development of a module for the SANE-GP.

*Phase-1*

Objective 1: A questionnaire on nurses’ knowledge about sexual assault examination-(KQSANE-I) will be developed based on the Robert F DeVellis method of tool development (
DeVellis, 2016), which includes item development, item pooling, content adequacy assessment, clarification of the items, refining the items, the administration of questionnaire (empirical testing after determining the scale for items and adequate sample size), item analysis, reliability assessment, and construct validity. The administration of the questionnaire will be conducted through a survey, and the data will be collected from 450 participants. Skill questionnaires and practice checklists will be developed along with the development of the SANE-GP module.

Objective 2: Delphi techniques of data collection with experts in the field of forensic science to develop a SANE-GP module for nurses.

*Phase-2*

Objective 3: The study proposes to have one group with a before and after experimental design with three follow-ups to evaluate the effectiveness of SANE-GP among nurses working in the hospital.

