### The plan for data analysis

The researchers will use statistical software by IBM (IBM SPSS Statistics, RRID:SCR_019096),
SPSS statistics 26 (Armonk, NY: IBM Corp) for the analysis. In Phase-I, the data will be summarised using descriptive statistics and will be presented in a summary table. The knowledge score will be assessed four times (one before SANE-GP and three follow-ups), and the scores will be compared and analysed with the help of time-series analysis. The skill of the participants will be assessed after the completion of each module, and the score will be described in tables. The practice of the random participants will be assessed and described.

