### Limitations

Although the study aims to develop the SANE program, it requires widespread acceptance across the hospitals in the country. The absence of policy changes and revision of existing guidelines are a few challenges that can block the nationwide implementation of SANE programs. Sustainable planning is also needed for the development of a platform that connects the SANEs across the country. The study is planned as an experimental design and does not involve any randomisation or control.

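### Skill is scored only after each module and there is no control group, so the plan can describe skill attained but cannot estimate the effectiveness of training on skill

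*Protocol article*

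**What the plan says.** Objective iii in the protocol article (Research objectives) is to "Explore the effectiveness of SANE-GP on the knowledge and skill regarding SAE". The section headed The study words the aim more strongly: to "investigate the effectiveness of multicomponent training in improving knowledge and skill". For this objective the Design section commits to "one group with a before and after experimental design with three follow-ups to evaluate the effectiveness of SANE-GP".

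The effectiveness assessment itself is tied to one instrument. Under Data collection (Phase-II), "The effectiveness of the SANE-GP will be assessed through administering KQSANE-I", and the next sentence reads "A pretest will be conducted on day one, and an immediate post-test will be conducted after the intervention". Data collection instruments defines KQSANE-I as the tool for knowledge. Follow-ups come at weeks 8, 16 and 24, and Expected outcomes assigns both the pre-training measurement and these follow-ups to knowledge.

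Skill has a different schedule. Data collection places the skill checklist at the end of each section of the module. Expected outcomes says "The skill will be assessed immediately after the completion of each module in the SANE-GP". The analysis plan says "The skill of the participants will be assessed after the completion of each module, and the score will be described in tables". Practice is assessed by the forensic expert with a separate checklist, after the programme, in participants chosen at random, and is likewise only described.

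Limitations states that the study "does not involve any randomisation or control".

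**The concern.** Effectiveness, and improvement still more plainly, needs a reference level: the same nurses before training, or comparable nurses without it. The plan supplies the first for knowledge and neither for skill. The before-and-after design that the Design section attaches to objective 3 is therefore delivered for only one of the two outcomes that the objective names.

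At stake is what the study may conclude. A tabulated post-module score is a sound description of what nurses can do at that point. It does not say how much of that ability the programme produced. Prior skill cannot be taken as nil: the demographic proforma records earlier experience of these examinations, the Phase-II inclusion criteria do not rule such experience out, and the Discussion says that nurses currently assist at them. A baseline that was not collected cannot be recovered by any later analysis.

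**Working it through.** **The plan's own figure.** The only Phase-II calculation is the sample size. With the inputs under Sample size (1.96 and 0.84; σ = 23.75; m = 3; ρ = 0.4; d = 7):

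n = (1.96 + 0.84)² × 23.75² × [1 + (3 − 1) × 0.4] / (3 × 7²) = 7.84 × 564.0625 × 1.8 / 147 = 54.15, rounded up to 55.

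Allowing for 25% non-response: 55 / 0.75 = 73.3, rounded up to 74. This agrees with the stated 74. The value m = 3 matches the three follow-ups, which are scheduled for knowledge only. Nothing in this point changes that number.

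**The measurement schedules side by side.**

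| | Knowledge | Skill | Practice |
|---|---|---|---|
| Instrument | KQSANE-I | Skill checklist | Practice checklist |
| Before training | 1 (day one) | 0 | 0 |
| After training | Weeks 8, 16 and 24, plus an immediate post-test under Data collection | Once at the end of each section or module | During later cases, randomly chosen participants |
| Comparator group | 0 | 0 | 0 |
| Planned analysis | Comparison over time | Tables | Description |

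**What can be estimated.** Write a nurse's score at the end of a module as S = P + G, where P is skill before the module and G is the gain. The plan observes S only. Any split of S into P and G fits the data equally well, so the mean of G is not identified, whatever the number of nurses. For knowledge, P is observed at the pretest and the change can be estimated.

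**Could something else in the plan serve as a baseline?**

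1. *The day-one pretest.* It follows directly on the sentence about KQSANE-I, which is a knowledge tool. Expected outcomes and the analysis plan mention a pre-training measurement for knowledge alone.
2. *The skill questionnaires mentioned under Design.* They are to be developed along with the module, but no section schedules them before training.
3. *Scores from earlier modules.* The 14 draft modules cover different content, so a score on one is not a baseline for another.
4. *The practice checklist.* It is a different checklist, used only after training and only in some participants. It cannot show change.

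None of the four supplies a reference level for skill.

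**The case against.** The strongest reply is that the analysis plan already treats skill descriptively. It promises tables with no test, contrast or threshold, effectiveness is formally tied to KQSANE-I, Expected outcomes speaks only of assessing skill, and objective iii opens with the word explore. On this view the plan is modest and only the wording of the aim and objective goes too far. That stands, and it is why rewording is enough. It does not remove the conflict, because the objective still asks about effectiveness and the aim still says improving.

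Three stronger readings are tempting, and the documents do not support them:

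- *A reader might infer that high skill scores will be reported as proof of effectiveness.* The protocol plans only to tabulate them. The fault is an objective that the data cannot answer, not a planned misreport.
- *A reader might infer that many nurses already have the skill.* The Introduction, Research gap and Discussion say that nurses lack forensic training, that nursing curricula omit it, and that only doctors may conduct the examination. On those premises substantial prior skill is less likely. It remains unmeasured and, since nurses assist, it is not shown to be zero.
- *A reader might infer that nothing will be learned about performance later on.* The practice checklist gives some information on performance after training, though no estimate of change. Retention of skill is not a stated objective.

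It could also be said that Limitations discloses the weakness. It discloses the lack of randomisation and control. It does not mention the missing skill baseline or narrow the objective. Nor is this detail left to a fuller document: the article fixes the timing of the skill assessment in three places.

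**Conclusion.** The point holds as a mismatch between objective and schedule. Skill has 0 pre-training measurements and 0 comparator groups, so the planned data give the level attained after each module and no estimate of change. One of the two outcomes named in objective iii therefore has no estimable effect. The conclusion rests on the schedule as written in Data collection, Expected outcomes and the analysis plan, which agree with one another, and on reading the day-one pretest as KQSANE-I only, as the text does.

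The knowledge analysis and the target of 74 are unaffected, and the post-module scores remain useful as description. This should be fixed, but it does not threaten the study as a whole. It is best settled now: the article reports that the study is still recruiting for Phase-I, and the skill tools are still to be developed.

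**What to change.** **Minimum.** Reword the aim (The study) and objective iii (Research objectives) to effectiveness on knowledge, and level of skill attained after each module. Make no effectiveness claim for skill or practice in reports. The schedule and the tables stay as they are, and the cost is nil.

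**Alternative, if effectiveness on skill is to remain an objective.** Score the same skill checklist, or a short core subset of practical stations, before training alongside the day-one pretest. Report the mean paired change with a 95% confidence interval. No extra nurses are needed for useful precision: with 55 to 74 pairs the half-width is about 1.96/√55 = 0.26 to 1.96/√74 = 0.23 standard deviations of the change score.

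This option has three costs:

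- *Time and assessors.* Seven sessions of 45 minutes already fill 7 × 45 = 315 minutes of each training day, and the article does not say who scores the skill checklist. If each of the 14 draft modules had one checklist, a full baseline in 74 nurses would be 74 × 14 = 1,036 scorings, which is why a core subset is worth considering.
- *Retest effect.* An untrained attempt at the checklist may itself raise the later score.
- *Interpretation.* Without a control group, a before-and-after change is still not a clean training effect and should be reported as a change.

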### The plan for data analysis

The researchers will use statistical software by IBM (IBM SPSS Statistics, RRID:SCR_019096),
SPSS statistics 26 (Armonk, NY: IBM Corp) for the analysis. In Phase-I, the data will be summarised using descriptive statistics and will be presented in a summary table. The knowledge score will be assessed four times (one before SANE-GP and three follow-ups), and the scores will be compared and analysed with the help of time-series analysis. The skill of the participants will be assessed after the completion of each module, and the score will be described in tables. The practice of the random participants will be assessed and described.

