## Abstract

The medico-legal care of victims of sexual assault is very challenging, and requires specific knowledge and skills. Professionals in the emergency departments of hospitals might not have specialised training in forensic science. Nurses have a very significant role in these settings, but they lack any formal forensic training. This study aims to develop a sexual assault nurse examiner-grounding program (SANE-GP) for Indian nurses to inculcate knowledge and skill regarding sexual assault examination. The study adopts a three-stage Delphi technique to develop the training module and uses a time-series design to evaluate the effectiveness of the program. A questionnaire on nurses’ knowledge on sexual assault examination (KQSANE-I) will be developed in phase-I and subsequently used in phase-II. The protocol of SANE-GP will help the medical community to implement the program across India. The implementation of SANE-GP can also help to start a sexual assault nurse examiner network.

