### Sample size

The sample size is calculated for Phase-I based on the item to response ratio of 1:10 given by
Schwab (1980). The KQSANE-I is planned to have a minimum of 44 items, hence, the sample size calculated for Phase-I is 450. For Delphi, seven experts will be recruited for participating in the study. The sample size calculated for Phase-II is based on the time series analysis using the formula n = [Z
_1-α/2_ + Z
_1-β_]
^2^ σ
^2^ [1 + (m − 1)ρ]/md
^2^ (where, n is the sample size, Z
_1-α/2_ at α = 0.05 = 1.96, Z
_1-β_ at 80% power = 0.84, σ = standard deviation (23.75), ‘m’= number of follow ups (3), ‘ρ’ = intraclass correlation (0.4), ‘d’ = clinically significant difference (7)). The sample size is calculated with an anticipatory non-response rate of 25% which is 74. The participants will be recruited through purposive sampling for SANE-GP.

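### The knowledge score is assigned to time-series analysis, but the data are a few repeated measurements on the same nurses with one pretest: name a within-nurse repeated-measures analysis and restate the power for its contrast

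*Protocol article*

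**What the plan says.** The plan for data analysis states: "The knowledge score will be assessed four times (one before SANE-GP and three follow-ups". It adds that the "scores will be compared and analysed with the help of time-series analysis", using SPSS 26. Skill and practice scores are only to be described, so this sentence carries the whole inferential analysis for Objective 3.

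The label also appears elsewhere. The abstract says that the study "uses a time-series design to evaluate the effectiveness of the program". The Sample size section says: "The sample size calculated for Phase-II is based on the time series analysis using the formula", and then gives a formula with an intraclass correlation of 0.4 and three follow-ups.

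The design itself is described differently. The Design section proposes "one group with a before and after experimental design with three follow-ups", and Limitations confirms that the study "does not involve any randomisation or control". The Phase-II part of Data collection reads: "A pretest will be conducted on day one, and an immediate post-test will be conducted after the intervention", and then: "Follow-ups will be conducted on the 8th, 16th, and 24th week after SANE-GP". That makes five knowledge assessments. The Expected outcomes section and the analysis section count four, without the immediate post-test.

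**The concern.** Time-series methods in the usual sense (ARIMA, interrupted time series) model one long sequence, with enough points before the intervention to establish its level, trend and autocorrelation. Here each nurse gives four or five scores, and only one precedes training. The information lies in the change within each nurse, replicated over nurses, and not in the length of a series.

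There is no control group, so the before-after comparison is the only evidence on effectiveness. If the label were followed literally, that comparison would rest on a model that the design cannot support, or on a handful of occasion means. If it is a loose name for something else, the reader cannot tell which model or which contrast will test the programme.

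**Working it through.** **1. The stated sample size.** Inputs from the Sample size section: z-values 1.96 and 0.84, σ = 23.75, m = 3, ρ = 0.4, d = 7, non-response 25%.

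- n = (1.96 + 0.84)² × 23.75² × [1 + 2 × 0.4] / (3 × 7²) = 7.84 × 564.06 × 1.8 / 147 = 54.15, so 55.
- 55 / 0.75 = 73.3, so 74.

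The figure of 74 reproduces. The formula is for the mean of three correlated measurements per person. The sample size therefore already treats the scores as repeated measures within nurses.

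**2. What a time-series model could estimate.** An interrupted time-series model has an intercept, a pre-training trend, a level change and a slope change. Take occasions at t = 0, 8, 16 and 24 weeks, with I = 0 before training and 1 after. At every occasion t = 8 × I + I × (t − 8), so the trend column is an exact combination of the other two. The design matrix has rank 3 for 4 parameters, and the pre-training trend is not identified. Adding the immediate post-test does not help, because there is still only one point before training.

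Reduced models on four occasion means can be fitted, but little is left over:
- intercept, step and post-training slope: 4 − 3 = 1 residual degree of freedom;
- intercept and step: 4 − 2 = 2.

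As an illustration, 10,000 trials were simulated with the protocol's σ, ρ and d, equal correlation between occasions and 55 nurses. The step model on four means had about 30% power, against 67% for a paired contrast and 68% for a mixed model on the same data. Its type I error was close to nominal (4.8%), so the cost is power.

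**3. Power of a within-nurse contrast.** Take the mean of weeks 8, 16 and 24 minus the pretest, with equal correlation ρ between occasions.

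- Variance per nurse = σ² × [(1 + 2ρ)/3 + 1 − 2ρ]. At ρ = 0.4 this is σ² × (0.6 + 1 − 0.8) = 0.8σ² = 451.25.
- The protocol's formula uses only the first term, 0.6σ².
- 55 evaluable: SE = √(451.25/55) = 2.86; 7/2.86 − 1.96 ≈ 0.48; power about 69%.
- 74 evaluable: SE = √(451.25/74) = 2.47; 7/2.47 − 1.96 ≈ 0.87; power about 81%.
- For 80%: 7.84 × 451.25 / 49 = 72.2, so 73 evaluable; 73 / 0.75 = 97.3, so 98 recruited.

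The answer depends on ρ:

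| ρ | Evaluable for 80% | Power with 55 |
|---|---|---|
| 0.3 | 85 | 62% |
| 0.4 | 73 | 69% |
| 0.5 | 61 | 76% |
| 0.6 | 49 | 85% |

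**The case against.** The best defence is that the authors use the term loosely. The only place where the article gives it content is the Sample size section, where it labels a repeated-measures formula with ρ = 0.4. Read together with the analysis section, this suggests that some repeated-measures analysis is intended. That is plausible, and it limits the finding. It does not remove it, because the named method still does not describe such an analysis. An article may leave model details to a fuller document, but the point here is what it states and not what it omits.

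Several stronger readings are tempting and are not supported:

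- *The plan ignores the pairing within nurses.* The article does not say how the scores enter the analysis. This would follow if occasion means were modelled, or if scores were pooled as independent, and it proposes neither. Error rates computed for a pooled analysis would not describe this plan.
- *The effect cannot be estimated.* Only a model with a pre-training trend fails, and the article does not propose one. A step model on occasion means can be estimated, though weakly.
- *Nurses with missed visits would be lost.* Occasion means would still use their available scores. Nor does the article say that its 25% non-response means missed visits.
- *Only a mixed model will do.* Repeated-measures ANOVA or generalised estimating equations would also respect the pairing.

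**Conclusion.** The concern holds in this form: the named method does not suit a single-group study with one pretest and a few follow-ups on the same nurses, and it does not match the repeated-measures basis of the protocol's own sample size. The conclusion about the method needs no numerical assumption.

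The power figures do. They assume that 23.75 is the standard deviation of a single score at every occasion, the pretest included, that all occasions are equally correlated at 0.4, and that the difference of 7 is the same at all three follow-ups. On those terms the within-nurse contrast has about 69% power with 55 evaluable nurses, not 80%. The article does not say what 23.75 is the standard deviation of. If it refers to change from pretest, and 0.4 to the correlation between changes, the formula already covers the pretest and the 80% would stand. The article should say which is meant.

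**What to change.** - In The plan for data analysis, replace the time-series wording with a within-nurse repeated-measures analysis. The preferred choice is a linear mixed model (the MIXED procedure in the SPSS already named), with time as a categorical factor including the pretest, and all available visits used. This keeps nurses whose follow-up is incomplete.
- Name the primary contrast, for example the mean of weeks 8, 16 and 24 minus the pretest, with its 95% confidence interval.
- Reconcile the five assessments in Data collection with the four in Expected outcomes and The plan for data analysis, and say whether the immediate post-test enters the model.
- In the abstract and the Sample size section, describe the design as single-group pre-post with repeated follow-up.
- State what 23.75 and 0.4 refer to, and restate the power for the chosen contrast.

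The wording changes cost almost nothing, and the article reports that Phase I is still recruiting. The power is the real cost. For the example contrast at ρ = 0.4, the authors must either accept about 69% with 55 evaluable nurses, or plan for 73 evaluable (98 recruited at 25% non-response), or justify a higher correlation.
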